### 2.9. Outcomes

The primary outcome includes the evaluation of changes in the gut and intra-tumoral microbiota composition and its relationship with the postoperative rate of anastomotic leakage and surgical site infection after the nutritional intervention. Secondary outcomes will include the determination of changes in SCFA levels in serum and feces, serum levels of inflammation markers, endotoxemia, and intestinal permeability, length of hospitalization after surgery, recurrence of CRC after surgery, response to adjuvant therapy, and post-surgical survival rates.

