## Abstract

Colorectal cancer (CRC) is the third most common cancer and the second cause of cancer death worldwide. Several factors have been postulated to be involved in CRC pathophysiology, including heritable and environmental factors, which are the latest to be closely associated with nutritional habits, physical activity, obesity, and the gut microbiota. The latter may also play a key role in CRC prognosis and derived complications in patients undergoing surgery. This is a single-center, open, controlled, randomized clinical trial, in patients with scheduled surgical intervention for CRC. The primary objective is to assess whether a pre-surgical nutritional intervention, based on a high-fiber diet rich in polyunsaturated fatty acids (PUFAs), can reduce disturbances of the gut microbiota composition and, consequently, the rate of post-surgical complications in patients with CRC. Patients will be randomized in a 1:1 ratio after receiving a diagnosis of CRC. In the control arm, patients will receive standard nutritional recommendations, while patients in the intervention arm will be advised to follow a high-fiber diet rich in PUFAs before surgery. Participants will be followed up for one year to evaluate the overall rate of postsurgical complications, recurrences of CRC, response to adjuvant therapy, and overall/disease-free survival.

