## 2. Methods

### 2.1. Study Objectives

The objective of this study is to evaluate whether a pre-surgical nutritional intervention based on a high-fiber diet rich in PUFAs can revert gut microbiota alterations, surgical site infections, and anastomotic leaks in patients with CRC undergoing elective surgery (colonic resection with anastomosis), compared to a control group following standard nutrition recommendations.

To achieve this objective, three major aims are defined:To determine the change in the gut and intra-tumoral microbiome composition, fecal and serum levels of short-chain fatty acids (SCFAs), and serum inflammation, endotoxemia, and intestinal permeability markers in CRC patients following a high-fiber diet rich in PUFAs in the preoperative phase, in comparison to the control group.To evaluate the rate of anastomotic dehiscence and surgical site infections after surgery (30 days of follow-up) in the intervention group, in comparison to the control group.To establish the length of hospitalization, recurrences of CRC, response to adjuvant therapy, and overall and disease-free survival after surgery (1 year of follow-up) in the intervention group, in comparison to the control group.

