### 2.11. Sample Size and Recruitment

Sample size calculation was based on expected differences in the rate of anastomotic dehiscence of CRC surgery. According to the literature, the anastomotic leak rate in CRC patients undergoing CRC surgery varies between 3% and 50%; therefore, we estimated that for a reduction in anastomotic leak from 30% to 10%, assuming a significance level of 5% and a β power of 0.8, 48 patients in each study group would be necessary. Considering a potential 10% of follow-up losses, 54 patients per group will be recruited.

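### The declared primary outcome bundles microbiota change with its relationship to leak and infection, while the sample size and the 80% power belong to a different quantity: leak rate by arm

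*Protocol article*

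**What the plan says.** Section 2.9 gives the primary outcome as "changes in the gut and intra-tumoral microbiota composition and its relationship with the postoperative rate of anastomotic leakage and surgical site infection". It names no microbiota measure and no comparison between arms. Leak and infection are not in its list of secondary outcomes.

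Section 2.11 begins: "Sample size calculation was based on expected differences in the rate of anastomotic dehiscence of CRC surgery". It assumes a fall from 30% to 10% and continues "assuming a significance level of 5% and a β power of 0.8, 48 patients in each study group would be necessary", then "Considering a potential 10% of follow-up losses, 54 patients per group will be recruited". It does not say whether the test is one- or two-sided.

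The main question is put differently elsewhere:

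- The Abstract's primary objective is whether the diet "can reduce disturbances of the gut microbiota composition and, consequently, the rate of post-surgical complications in patients with CRC".
- Section 2.1 states one objective covering gut microbiota alterations, surgical site infections and leaks against control. It then lists three aims. The microbiome comes first, and the second is "To evaluate the rate of anastomotic dehiscence and surgical site infections after surgery (30 days of follow-up) in the intervention group", compared with control.
- Section 2.15 refers to primary outcomes in the plural and sets p < 0.05 for all statistical analyses.

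**The concern.** A primary outcome should be one quantity with one contrast, and the sample size should be calculated for it. Here the declared quantity and the sized quantity differ. In Section 2.9 leak enters only as something that microbiota change is related to. The comparison of leak rates between arms, which is the one comparison with a power statement, is ranked as neither primary nor secondary there.

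Two things are at stake. First, a reader of the final report would take the 80% power as supporting the declared primary outcome, when no power has been worked out for it. Second, relating microbiota change to leak compares patients by a variable measured after allocation (the day before surgery, Section 2.13.1). Randomisation does not protect that comparison, so it cannot by itself carry the causal step in the Abstract's objective, from less microbiota disturbance to fewer complications. With several components and no stated order, it is also unclear which result would decide the trial.

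**Working it through.** **Inputs.** Leak 30% (control) and 10% (intervention), significance level 5%, power 0.8, 48 per group, 54 after 10% losses (Section 2.11). Allocation 1:1 (Section 2.12). Chi-square test for categorical variables and p < 0.05 (Section 2.15).

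**1. Reproducing the plan's figure.** Pooled-variance formula, mean rate 0.20:

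n = [z_α·√(2·0.20·0.80) + z_β·√(0.30·0.70 + 0.10·0.90)]² / 0.20²

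- One-sided: (1.645·0.5657 + 0.842·0.5477)² / 0.04 = 48.4, or 49 rounded up. This agrees with 48 to within one patient.
- Two-sided: (1.960·0.5657 + 0.842·0.5477)² / 0.04 = 61.6, or 62.
- Other two-sided versions: 59 unpooled, 60 arcsine, 72 with continuity correction. None gives 48.
- Losses: 48 / 0.9 = 53.3, or 54, which matches. For 62 per group, 62 / 0.9 = 68.9, or 69.

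So the calculation concerns leak by arm and nothing else, and 48 comes out only as a one-sided figure.

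**2. Power for leak by arm.** Power = Φ{[0.20·√n − z_α·0.5657] / 0.5477}

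| Evaluable per group | One-sided 5% | Two-sided 5% |
|---|---|---|
| 48 | 79.7% | 69.3% |
| 54 (no losses) | 83.8% | 74.5% |

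Exact enumeration of the two-sided chi-square test without continuity correction gives 71.5% and 76.3%, so the approximation is adequate.

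**3. Information behind the relationship.** Expected leaks at the plan's own rates: 48·0.30 + 48·0.10 = 14.4 + 4.8 = 19.2 in 96 patients. The article gives no power for an association based on this number.

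**4. False-positive risk if the named components are tested separately.** Section 2.9 names four: gut microbiota, intra-tumoral microbiota, leak and infection. With k independent tests at 0.05 the risk is 1 − 0.95^k:

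- k = 2: 9.8%
- k = 3: 14.3%
- k = 4: 18.5%

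Independence is an assumption. Positive correlation lowers the figure. Using several measures within a compartment raises it, and Section 2.13.3 lists composition, diversity, richness and functionality without choosing one.

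**5. The statements side by side.**

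| Place | Main question |
|---|---|
| Abstract | Gut microbiota and, as a consequence, post-surgical complications |
| Section 2.1 | Gut microbiota, infections and leaks; leak and infection rates by arm are the second aim |
| Section 2.9 | Gut and tumour microbiota and their relationship with leak and infection |
| Section 2.11 | Leak by arm alone |

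No two of the four are the same.

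**The case against.** The best defence is that leak by arm is one of several primary outcomes, badly phrased. Leak and infection stand in the primary-outcome sentence and not among the secondary outcomes. Section 2.1 puts both in the objective against control and gives their rates by arm as the second aim, and Section 2.15 uses the plural. This stands in part. A reader might infer that the randomised leak comparison is missing from the plan, and the text does not support that: the comparison is planned, but its rank is unclear. The mismatch with Section 2.11 remains, because Section 2.9 declares a relationship and Section 2.11 sizes a difference between arms.

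A second defence is that the order of testing is commonly left to a statistical analysis plan, which is not shown. This also stands in part. A reader might infer that the trial has no control of its primary error rate, or that success on any component would count as success of the trial. The article sets one general threshold and does not exclude a hierarchy, and nowhere does it define success that way. The 18.5% is therefore conditional. An analysis plan could supply an order, but it would not by itself reconcile Sections 2.9 and 2.11.

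A reader might also count composition, diversity and richness in both compartments plus leak and infection, eight tests in all, and quote 1 − 0.95^8 = 34%. The documents do not support that count. Section 2.9 names composition only; the other measures come from the laboratory methods and have no primary status. Measures taken from the same samples are also unlikely to be independent.

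Finally, the article does not claim that the association would prove that diet lowers leak, since the second aim asks that through the arms. That is fair. The criticism is only that the association is what has been labelled primary.

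**Conclusion.** The concern holds as an inconsistency between the declared primary outcome and the quantity that was sized. The 80% power applies to leak by arm under a one-sided 5% test and not to the outcome in Section 2.9, for which no power is given. The relationship between microbiota and leak is observational and would rest on about 19 events if the assumed rates are right.

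The false-positive risk is a secondary part of the point: about 18.5% if the four named components were each tested at 0.05, unordered and independent, and different if any of those conditions fails.

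The power figures assume leak rates of 30% and 10%. The two-sided reading is also an assumption, made because a chi-square test at p < 0.05 is two-sided by usual practice and the article does not say otherwise.

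**What to change.** - In Section 2.9, name one primary outcome: the proportion of patients with anastomotic leak within 30 days of surgery, compared between the randomised arms. It is already the basis of the sample size and is already collected (Section 2.13.9 and Table 1).
- Make surgical site infection and the between-arm change in gut microbiota secondary outcomes in a fixed testing order, with one microbiota measure chosen in advance.
- Label the microbiota–leak association exploratory.
- Bring the Abstract and Sections 2.1, 2.9 and 2.15 into line with this.
- In Section 2.11, state the sidedness and restate the power. At two-sided 5% it is about 69% with 48 evaluable per group and about 75% with 54. Keeping 80% two-sided would need 62 evaluable per group, or 69 recruited, which is 15 more per group than planned.

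**Cost.** The wording needs an amendment and no new measurements, and is best made before outcome data by arm are seen. Microbiota becomes a secondary claim. The sponsor must either accept the lower two-sided power or recruit more patients.

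**Alternative.** Co-primary outcomes with a split significance level would also remove the inconsistency, at a higher price. For leak at two-sided 0.025, 75 per group are needed (84 with losses). With four co-primaries at 0.0125, 88 are needed (98 with losses).

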### 2.8. Intervention

Patients will be randomized in a 1:1 ratio after receiving a diagnosis of CRC during endoscopic evaluation (Figure 1). Patients included in the control arm will receive standard nutritional recommendations, while patients in the intervention arm will be advised to follow a high-fiber diet rich in PUFAs (total dietary intake of at least 30 g of fiber per day, and at least 3 g of PUFAs per day from food, not supplements) for at least 4 weeks before surgery.

Participants may withdraw or revoke consent at any time without giving explanations and without any prejudice to them. Individuals who drop out of the study will not undergo further follow-up or be replaced by new subjects. Subjects may be withdrawn if researchers/clinicians consider that the participant can no longer comply with all the requirements of the study, or if any of the procedures is considered as potentially harmful to the subject.

As this is a prospective longitudinal study, some patients might find it difficult to follow the nutritional recommendations. Nevertheless, thanks to the close monitoring of the expert nutritionist, we will manage to reduce the abandonment percentage to a minimum. We plan to provide a written protocol in lay terms for the study participants, including a detailed handbook that they can use as a guide, and they will have full access to the nutritionist via telephone or weekly individual meetings.

Participants will not be allowed to consume any dietary supplement including pre- or probiotics during the intervention period.

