#### 2.13.9. Assessment of Postoperative Follow-Up and Recovery

Patients will be carefully monitored for any signs of anastomotic leak and surgical site infection symptoms (fever, leukocytosis, severe abdominal pain, etc.) within 30 days after surgery. Diagnosis of anastomotic leakage will be confirmed by radiological examination (CT scan or MRI), clinical examination, detection of serum biomarkers (CRP and procalcitonin), and post-operative endoscopy (if required). Post-operative surgical site infections will be assessed using the ASEPSIS score system. In addition, the recruited patients will be followed up for at least one year in order to evaluate recurrences of CRC, response to adjuvant therapy, and overall/disease-free survival.

Subjects will be followed up by phone every week during the intervention and for a month after surgery, and every month until the completion of the trial. Data collected from participants that withdraw from the study will be retained following the Office of Human Research Protections. No financial incentives will be provided to any of the participants.

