### 2.15. Statistical Methods

The analyses of this study will follow the intention-to-treat (ITT) principles. All statistical analyses will be performed with SPSS v.22.0 software (SPSS Inc., Chicago, IL, USA), considering a level of *p* < 0.05 as statistically significant. Normality of distributions will be assessed using the Shapiro–Wilk test. A descriptive analysis of the variables will be carried out with punctual estimation and a confidence interval for 95% of security, treating the continuous variables as means, standard deviation, or medians according to the distribution of the variable. Categorical variables will be presented in frequencies and percentages. Continuous variables will be compared by Student’s “t” test and by analysis of variance (ANOVA), depending on the existence of 2 or more groups in each comparison. The association between categorical variables will be analyzed using the chi-square test. Studies of correlations between the variables will be carried out using the Pearson or Spearman test based on the normality of the analyzed variables.

Per protocol analysis will be performed within participants that fulfill the intervention. This approach will be used only for the primary outcomes and will be treated as a secondary analysis. In the case of a relevant number of missing values, multiple imputation or pattern mixture models will be used.

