## Figures and Tables

**Figure 1 jcm-11-03613-f001:**
[figure not shown]
Trial flowchart of the intervention.

**Table 1 jcm-11-03613-t001:** Assessment schedule.

	STUDY PERIOD						
	Enrolment	Allocation	Post-Allocation				Close-Out
TIMEPOINT	t_−1_	t_0_	t_1_	t_2_	t_3_	t_4_	t_5_
ENROLLMENT:							
Eligibility screen	X						
Informed consent	X						
Inclusion criteria	X						
Exclusion criteria	X						
Allocation		X					
INTERVENTIONS:							
High-fiber diet rich in PUFAs			X	X			
Standard nutritional recommendation			X	X			
ASSESSMENTS:							
Anthropometric measurements	X						
Medication	X						
Food Frequency Questionnaire (FFQs)	X						
Tumor biopsies		X		X			X
Fecal samples			X	X			X
Blood samples			X	X			X
Anastomotic leak					X		
Surgical site infections					X		
CRC recurrence						X	
Response to adjuvant therapy						X	
Disease-free survival						X	
Quality of life questionnaire						X	

t_−1_: At baseline colonoscopy; t_0_: At baseline screening colonoscopy; t_1_: Four weeks pre-surgery intervention; t_2_: Day before surgery; t_3_: 30 days post-surgery; t_4_: 1–12 months after surgery (follow-up); t_5_: 12 months after surgery.

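### Survival and recurrence are dated from surgery although randomisation and the whole diet come before it, and no clinical event in between is an outcome

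*Protocol article*

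**What the plan says.** Section 2.8 sets the moment of allocation: "Patients will be randomized in a 1:1 ratio after receiving a diagnosis of CRC during endoscopic evaluation". The intervention arm is then advised to follow the diet "for at least 4 weeks before surgery". Section 2.10 describes four weeks of intervention, 12 months of follow-up and 13 months in total.

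The clinical outcomes start later. Section 2.9 lists post-operative hospital stay, then "recurrence of CRC after surgery, response to adjuvant therapy, and post-surgical survival rates". The third aim in section 2.1 likewise places overall and disease-free survival after surgery, with one year of follow-up. Section 2.13.9 monitors leak and "surgical site infection symptoms (fever, leukocytosis, severe abdominal pain, etc.) within 30 days after surgery". In Table 1, t2 to t5 are all dated by the operation, and the first clinical outcome appears at t3, 30 days after surgery.

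Three other statements bear on the point:

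- Section 2.13.9 already provides contact before surgery: "Subjects will be followed up by phone every week during the intervention and for a month after surgery".
- Section 2.8 allows the team to withdraw a participant who can no longer meet the study's requirements, and drop-outs are not followed further.
- Section 2.15 states: "The analyses of this study will follow the intention-to-treat (ITT) principles". It offers multiple imputation or pattern mixture models if many values are missing.

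**The concern.** Randomisation protects a comparison that starts at randomisation. Here the survival clock starts at least four weeks later, once the allocated diet is over. Survival from surgery compares those who lived to be operated on, and that group is formed after allocation.

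Leak and infection are a different case. They can exist only after an operation, so conditioning on surgery is unavoidable. The reader then needs to see how many patients in each arm reached the planned resection with anastomosis, and why the others did not. The plan lists no outcome that would show this. Because section 2.12 leaves staff unblinded, decisions to withdraw a patient or change the operation are made with the arm known.

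**Working it through.** **Time origins side by side**

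| Item | Origin or window | Section |
|---|---|---|
| Randomisation | at endoscopic diagnosis | 2.8, 2.12 |
| Diet | at least 4 weeks, all before surgery | 2.8, 2.10 |
| Leak, surgical site infection | 30 days from surgery | 2.1, 2.13.9, Table 1 |
| Recurrence, overall and disease-free survival | up to 1 year from surgery | 2.1, 2.9, Table 1 |
| Clinical events between randomisation and surgery | none listed | 2.9, Table 1 |
| Analysis principle | intention-to-treat | 2.15 |

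A death in the second week after randomisation belongs to an allocated patient but cannot be an event in a quantity that starts at surgery. Imputation does not repair this: post-surgical survival is undefined for that patient, not missing, and a leak cannot sensibly be imputed where there is no anastomosis.

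**The plan's own sample size.** Section 2.11 gives 48 per group for leak rates of 30% and 10%, and 54 after 10% losses. 48 / 0.90 = 53.3, rounded up to 54, agrees. The 48 is reproduced to within two patients only with a one-sided 5% test (47 to 49 by three formulas). That is a separate matter and is not used as an argument here.

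**Effect on survival.** Let *k* patients of 54 in one arm die before surgery, and let *S* be survival among those operated on, taking everyone else as operated on and followed.

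- From surgery, the arm shows *S*.
- From randomisation, it shows *S* × (54 − *k*)/54.
- The difference is *S* × *k*/54, which is at most *k*/54.

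For *k* = 1 this is at most 1/54 = 1.9 points. For *k* = 5 it is at most 5/54 = 9.3 points. The range 1 to 5 is assumed, since the documents give no rate. The upper end distorts the comparison by that much only if all five fall in one arm and none in the other.

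**Effect on the leak rate.** One lost patient moves it less. A 30% rate is about 16 of 54, or 29.6%. Leaving out one patient who would not have leaked gives 16/53 = 30.2% (up 0.6 points). Leaving out one who would have leaked gives 15/53 = 28.3% (down 1.3 points). The planned leak difference is 20 points, or 0.20 × 54 = 10.8 patients per arm.

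**Selection, under assumed figures.** Suppose the diet has no effect and the true leak risk is 30%. If a share *q* of one arm does not reach anastomosis and those patients would have had risk *r*, that arm shows (0.30 − *q r*)/(1 − *q*):

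| *q* | *r* = 30% | *r* = 60% | *r* = 100% |
|---|---|---|---|
| 5% | 30.0% | 28.4% | 26.3% |
| 10% | 30.0% | 26.7% | 22.2% |

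There is no bias unless the missing patients differ in risk. Even with *q* = 10% and double the risk, the shift is 3.3 points.

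**Power.** 54 × 0.90 = 48.6 evaluable patients per arm gives 80.1% (one-sided 5%). If a further 5% are not evaluable, 46.2 remain and power is 78.3%. The loss is modest; the issue is selection.

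**The case against.** The strongest reply is that rules for such patients commonly sit in an analysis plan or full protocol that is not shown, and that the article already states intention-to-treat, offers imputation and allows 10% for losses. This stands as far as the counting rule for leak and infection goes: its absence alone is no finding. It does not cover the time origin of survival and recurrence, which the article itself fixes in its aims, outcomes and schedule. Nor can a later plan report events by arm that were not recorded.

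Several stronger readings are tempting but unsupported:

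- **That every visit is counted from surgery.** Baseline contacts and weekly calls come before it.
- **That nothing in the intervention period is an outcome.** Changes in microbiota, short-chain fatty acids and inflammation markers are. Only clinical events are absent.
- **That emergency or unresectable cases drop out entirely.** A patient operated on early, or found unresectable at operation, still has a surgery date. Section 2.13.9 does not limit its monitoring to elective operations, although the objective in section 2.1 does name elective resection with anastomosis.
- **That the plan excludes non-operated patients.** No section says so. They are left without a defined outcome.
- **That a harm of the diet would improve its apparent result.** This is possible in principle, but no figure in the documents supports it.

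The population also argues for a small effect: stage I–III, aged 18 to 80, cleared for elective major surgery, and without cardiac, chronic liver or chronic kidney disease.

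**Conclusion.** The concern holds in a limited form. Dating survival and recurrence from surgery conflicts with the stated intention-to-treat principle, because the whole intervention falls before the clock starts. The absence of any pre-surgical clinical outcome also means that unequal progress to the planned operation would not be seen.

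The size is unknown. It is bounded by 1.9 points of survival per uncounted death in an arm of 54, and it affects the comparison only so far as the arms differ. The larger figures above rest on assumed numbers of patients and assumed risks. The bias is probably small here and the power loss modest. The change is worth making because it costs little, removes an avoidable selection after randomisation and adds safety information on the diet period.

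**What to change.** In sections 2.1, 2.9 and 2.13.9 and Table 1:

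1. Measure overall and disease-free survival from randomisation in all randomised patients, with death before surgery as an event. State how a patient who is never resected counts for disease-free survival. Treating that as an event is one option but a debatable definition, so the sponsor should choose and record it.
2. Keep following patients who have no operation to the 13-month end of trial, using randomisation to date their contacts.
3. Apply the 30-day leak and infection assessment after whatever colorectal operation is performed, and reconcile the objective in section 2.1 (elective resection with anastomosis) with the unrestricted monitoring in section 2.13.9.
4. Record emergency admission or operation, cancelled surgery, operation without anastomosis and death before surgery, using the existing weekly calls. Report them by arm beside the leak result.

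The cost is protocol wording and a few extra data fields. Survival figures will look slightly less favourable, and non-elective cases may add some noise to the leak and infection rates.
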